	2. Immunogenicity: To describe the transplacental antibody transfer of SARS-CoV-2 antibodies among individuals vaccinated during pregnancy, overall and by vaccine type and platform.	• GMT and ratio of cord blood to maternal serum IgG ELISA and Neut antibodies overall and by vaccine type and platform.	• GMTs and ratio of cord blood to maternal serum and 95% CIs will be calculated in Group 1.
	3. Immunogenicity: To describe kinetics and durability of serum SARS-CoV-2 antibodies in infants of mothers vaccinated during pregnancy, by vaccine type and platform.	• GMT of serum IgG ELISA and Neut antibodies at birth (cord blood) and at approximately 2 and 6 months of age in all infants, by vaccine type and platform.	• GMTs and 95% CIs will be calculated in Group 3. Plots such as reverse cumulative distributions or longitudinal presentations of GMTs will be presented.
**Secondary**	1. Safety: To describe pregnancy outcomes in individuals who receive COVID-19 vaccine during pregnancy or postpartum, and their infants, by vaccine type and platform.	• Frequency of maternal and infant outcomes vs. background rates in the US, overall and by vaccine type and platform.	• A comparison of frequencies to background rates will be reported in Groups 1–4 (no formal statistical testing).
	2. Immunogenicity: To evaluate immune responses and durability of antibodies in individuals who received different COVID-19 vaccines during pregnancy or postpartum compared to non-pregnant populations of women of childbearing age and to a correlate of protection (if available), by vaccine type and platform.	• GMT of serum IgG ELISA and Neut antibodies after vaccination in pregnancy or postpartum vs. mean titers achieved by non-pregnant participants in clinical trials and to a correlate of protection if available, by vaccine type and platform.	• One sample t-tests will be done in Group 1.

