	6. Immunogenicity: To describe the kinetics and durability of maternal serum antibodies following receipt of COVID-19 vaccine in individuals vaccinated postpartum, by vaccine type and platform.	• Postpartum individuals: GMT of serum IgG ELISA and Neut SARS-CoV-2 antibodies pre- and/or post-vaccination, and at approximately 2, 6, and 12 months after delivery, overall, and by vaccine type and platform.	• GMTs and 95% CIs will be calculated in Group 3. Plots such as reverse cumulative distributions or longitudinal presentations of GMTs will be presented.
	7. Immunogenicity: To describe the kinetics and durability of serum SARS-CoV-2 antibodies in infants of individuals vaccinated postpartum, by vaccine type and platform.	• GMT of serum IgG ELISA and Neut antibodies at approximately 2 and 6 months of age in infants of postpartum individuals, overall and by vaccine type and platform.	• GMTs and 95% CIs will be calculated in Group 4. Plots such as reverse cumulative distributions or longitudinal presentations of GMTs will be presented.
**Exploratory**	1. To describe the effectiveness of COVID-19 vaccines against maternal COVID-19 infection during pregnancy and postpartum.	• Incidence of laboratory confirmed COVID-19 and severity of disease during study participation assessed through passive surveillance in individuals vaccinated during pregnancy or postpartum vs. rates in unvaccinated population of women of childbearing age, overall and by vaccine type and platform.	• Incidence rates and 95% CIs will be calculated in Groups 1 and 3.
	2. To describe the effectiveness of maternal antibodies to provide protection against SARS-CoV-2 infection/symptomatic disease/severity in infants in the first 12 months of life.	• Incidence of laboratory confirmed COVID-19 and severity of disease during study participation assessed through passive surveillance in infants of individuals vaccinated in pregnancy or postpartum vs. background rates in infants of unvaccinated population, overall and by vaccine type and platform.	• Incidence rates and 95% CIs will be calculated in Groups 2 and 4.

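### Exploratory objective 2 measures infant COVID-19 over 12 months with no age split, which would understate early protection if maternal antibody wanes, and its analysis cell names the wrong groups

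*Protocol article*

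**What the plan says.** Table 5, Exploratory objective 2, reads: "To describe the effectiveness of maternal antibodies to provide protection against SARS-CoV-2 infection/symptomatic disease/severity in infants in the first 12 months of life". Its endpoint is "Incidence of laboratory confirmed COVID-19 and severity of disease during study participation assessed through passive surveillance in infants of individuals vaccinated in pregnancy or postpartum", compared "vs. background rates in infants of unvaccinated population, overall and by vaccine type and platform". The analysis cell says only: "Incidence rates and 95% CIs will be calculated in Groups 2 and 4". None of these cells mentions infant age or time since birth.

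The infant antibody endpoints in the same table cover a shorter span. Primary objective 3 measures serum antibody "at birth (cord blood) and at approximately 2 and 6 months of age in all infants", for mothers vaccinated in pregnancy. Secondary objective 7 measures it at about 2 and 6 months for infants of mothers vaccinated postpartum.

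The text is wider than the table. The opening paragraph of Methods has mothers and infants followed to 12 months with periodic immunogenicity sampling. The Follow-up section lists a 12-month visit for women and infants and has blood drawn for antibody assays at every routine visit.

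The list of analysis groups under Statistics defines Group 1 as women vaccinated in pregnancy, Group 2 as women vaccinated postpartum, Group 3 as infants of Group 1 mothers (about 200 per vaccine type) and Group 4 as infants of Group 2 mothers (about 65 per vaccine type).

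**The concern.** Antibody acquired before birth is not renewed from that source, so any protection it gives would be expected to be strongest early and to fall with age. A rate taken over the whole first year mixes the two phases. Half of that year (6 of 12 months) lies after the last infant antibody endpoint in Table 5. A substantial early effect could therefore be reported as a weak one.

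The row also brings together two kinds of infant. Vaccination after delivery cannot give the infant vaccine-induced antibody across the placenta. Table 5 keeps the two sets apart for antibody kinetics, and protection through breast milk has its own objective (Exploratory 3). The endpoint of Exploratory 2 nevertheless names both together, and its analysis cell points to a group of women and leaves out the infants most relevant to the question.

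The Background section expects the results to inform policy and personal decisions and offers the design as a template, so a figure that averages away early protection could mislead beyond this study.

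**Working it through.** **Reproducing a plan figure.** There is none. The document gives no incidence, effect size, event count or precision target for this objective. All rates and effects below are assumptions chosen to show direction and range.

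**Dilution.** Let VE_e be protection in months 0 to 6, VE_l protection in months 6 to 12, and r the background incidence in months 6 to 12 divided by that in months 0 to 6. With equal person-time in each half:

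12-month protection = 1 − [(1 − VE_e) + r(1 − VE_l)] / (1 + r)

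With VE_e = 0.60 and VE_l = 0:

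- r = 1: 1 − (0.40 + 1.00)/2 = 0.30
- r = 0.5: 1 − (0.40 + 0.50)/1.5 = 0.40
- r = 2: 1 − (0.40 + 2.00)/3 = 0.20

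Other assumptions, at r = 1:

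- VE_e = 0.40, VE_l = 0: 0.20
- VE_e = 0.80, VE_l = 0: 0.40
- VE_e = 0.60, VE_l = 0.20: 1 − (0.40 + 0.80)/2 = 0.40

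In each case the 12-month figure lies below the early one.

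**Precision of an age split.** Take one vaccine type with 200 Group 3 infants, r = 1, VE_e = 0.60, VE_l = 0, and background rates treated as known. Expected cases E are 200 × annual rate × fraction of the year. Exact Poisson 95% limits for observed/expected are χ²(0.025; 2O)/(2E) and χ²(0.975; 2O + 2)/(2E), where O is the number of observed cases.

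| Assumed annual background | 0–6 months: O/E | Ratio (95% CI) | 0–12 months: O/E | Ratio (95% CI) |
|---|---|---|---|---|
| 5% | 2/5 | 0.40 (0.05–1.44) | 7/10 | 0.70 (0.28–1.44) |
| 10% | 4/10 | 0.40 (0.11–1.02) | 14/20 | 0.70 (0.38–1.17) |
| 20% | 8/20 | 0.40 (0.17–0.79) | 28/40 | 0.70 (0.47–1.01) |

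The early band has a relatively wider interval (at 20%, 0.79/0.17 = 4.6-fold against 1.01/0.47 = 2.1-fold), but it is centred on the effect of interest. At 20% background the early band excludes no effect and the 12-month rate just fails to. At 5% and 10% neither does.

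**Groups.** Set against the list under Statistics, the analysis cell of Exploratory 2 covers women vaccinated postpartum (Group 2) and their infants (Group 4). Other rows suggest a numbering slip: Secondary 6, which concerns women vaccinated postpartum, cites Group 3, and Exploratory 1, which concerns women, cites Groups 1 and 3. Primary 3, by contrast, uses Group 3 correctly for infants. Table 5 thus uses Group 3 in two senses.

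**Entry age.** Under Methods, postpartum women may be enrolled within the first 2 months after delivery, with their infants. An infant entering at 2 months contributes at most 6 − 2 = 4 months to a 0 to 6 month band, so Group 4 person-time must start at enrolment, not at birth.

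**The case against.** The strongest reply is that Table 5 sets an observation window and does not forbid reporting by age. It promises incidence rates, further detail is deferred to an analysis plan that is not at hand, and age bands for an exploratory rate are ordinary analysis-plan material. That stands in part: a single collapsed rate is an inference from silence. But the stated endpoint, window and combined population are what the document fixes, and none of them points the analyst to age.

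A reader might go further in three ways that the document does not support.

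- *Infant antibody is not followed after 6 months.* Only the Table 5 endpoints stop there. Methods and Follow-up describe sampling to 12 months, and the schedule tables that could settle it are not reproduced. The passages need reconciling.
- *The study could not say how long protection lasts.* Dates of confirmed illness and details of the birth are collected, so analysis by age is possible.
- *All infants will be pooled.* One could combine about 200 + 65 = 265 infants per vaccine type and, assuming no protection in the 65, cut the 30% to 0.30 × 200/265 = 23%. But the word overall may well mean across vaccine types, Groups 3 and 4 are defined separately, and the cell as written omits Group 3. That pool is not stated.

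It is also fair that this is a descriptive objective resting on passive surveillance and external rates, with no test or decision attached.

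**Conclusion.** The point holds as a minor one. As written, the row describes protection over 12 months without an age split. If protection wanes, that figure understates early protection. The direction follows from averaging; the size does not come from the document. Under an assumed 60% early and no late protection, the 12-month figure is 30%, and it runs from 20% to 40% as the late-to-early ratio of background incidence goes from 2 to 0.5. If 20% protection persists late, it is 40% with constant incidence.

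The group numbers in the analysis cell are wrong on the face of the document and need correcting whatever is decided about age bands. The pattern across rows suggests a slip, not an intention to leave out infants of mothers vaccinated in pregnancy.

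No primary or secondary result is affected.

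**What to change.** - In Exploratory objective 2, report person-time incidence by infant age band, for example 0 to under 6 and 6 to 12 months, each against background rates for the same ages.
- Start person-time for postpartum-cohort infants at enrolment, since they may enter up to about 2 months after birth.
- Report Groups 3 and 4 separately, and replace Groups 2 and 4 in the analysis cell with Groups 3 and 4. Check the group numbers in Secondary 6 and in Exploratory 1 and 3 at the same time.
- Keep the 12-month figure as a summary.
- Reconcile the infant antibody time points in Table 5 with the sampling to 12 months described in Methods and Follow-up.

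The cut points are a choice. Narrower bands cost more: with 200 infants, a 20% annual background and 60% protection, 0 to under 3 months gives 4 observed against 10 expected cases, a ratio of 0.40 with 95% CI 0.11 to 1.02.

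The change is to wording and analysis only, and no new data are needed beyond the illness dates and birth details already collected. The downside is fewer cases per band and wider intervals. Age-matched background rates must also be available.

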	3. Immunogenicity: To assess the effect of gestational age at vaccination (trimester of gestation), maternal age, health and risk status, on immune responses and durability of antibodies in individuals who receive different COVID-19 vaccines during pregnancy or post-partum, by vaccine type and platform.	• GMT of serum IgG ELISA and Neut antibodies after vaccination in pregnancy by gestational age at vaccination (trimester of gestation) and interval between vaccination and delivery, by vaccine type and platform. GMT of serum IgG ELISA and Neut antibodies after vaccination in pregnancy or postpartum by maternal age, health status, and risk status (e.g., occupation, priority vaccination group) overall and by vaccine type and platform.	• GMTs and 95% CIs will be calculated for Group 1 by strata. Student’s t-tests and linear regression (controlling for potential confounders) will be used to compare strata.
	4. Immunogenicity: To describe the transplacental antibody transfer of SARS-CoV-2 antibodies among individuals vaccinated during pregnancy, by gestational age at vaccination, by interval from vaccination to delivery and maternal age, health and risk status, overall and by vaccine type and platform.	• GMT and ratio of cord blood to maternal serum IgG ELISA and Neut antibodies at delivery by gestational age at vaccination (trimester of gestation) and interval between vaccination and delivery, overall and by vaccine type and platform. • GMT and ratio of cord blood to maternal serum IgG ELISA and Neut antibodies at delivery by maternal age, health status, and risk status, overall and by vaccine type and platform.	• GMTs and ratios of cord blood to maternal serum and 95% CIs will be presented for Group 1 by strata. Student’s t-tests and linear regression (controlling for potential confounders) will be used to compare strata.
	5. Immunogenicity: To describe the kinetics of SARS-CoV-2 antibodies in breast milk of mothers who received vaccine during pregnancy or postpartum, overall and by vaccine type and platform.	• GMT of IgG and immunoglobulin A (IgA) ELISA and Neut antibodies in breast milk at approximately 2 weeks, and 2, 6, and 12 months postpartum, in individuals vaccinated during pregnancy or postpartum, overall and by vaccine type and platform.	• GMTs and 95% CIs will be calculated in Group 1. Plots such as reverse cumulative distributions or longitudinal presentations of GMTs will be presented.

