	3. To describe the effectiveness of breast milk antibodies to provide protection against SARS-CoV-2 infection/symptomatic disease/severity in infants in the first 12 months of life.	• Incidence of laboratory confirmed COVID-19 and severity of disease during study participation through passive surveillance in breastfed infants vs. not breastfed infants, by vaccine type and platform. • Incidence of laboratory confirmed COVID-19 and severity of disease during study participation through passive surveillance in breastfed infants of individuals vaccinated during pregnancy vs. postpartum, overall and by vaccine type and platform.	• Incidence rates and 95% CIs will be calculated in Groups 2 and 4.

*Abbreviations*: *GMT* Geometric Mean Titer, *IgG* immunoglobulin G, *ELISA* enzyme-linked immunosorbent assay, *Neut* neutralizing, *IgA* immunoglobulin A

^a^Pregnant individuals: pre- and/or post-vaccination, at delivery, and at approximately 2, 6, and 12 months postpartum

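### Exploratory objectives 2 and 3 promise the effectiveness of maternal and breast milk antibodies, but their three contrasts measure maternal vaccination, feeding and vaccination timing, and none uses a titer

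*Protocol article*

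**What the plan says.** All of this is in the Statistics section of the protocol article, Table 5.

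- **Exploratory 2, objective:** "To describe the effectiveness of maternal antibodies to provide protection against SARS-CoV-2 infection/symptomatic disease/severity in infants in the first 12 months of life".
- **Exploratory 2, endpoint:** incidence and severity of laboratory-confirmed COVID-19 "in infants of individuals vaccinated in pregnancy or postpartum vs. background rates in infants of unvaccinated population".
- **Exploratory 3, objective:** "To describe the effectiveness of breast milk antibodies to provide protection against SARS-CoV-2 infection/symptomatic disease/severity in infants".
- **Exploratory 3, first endpoint:** the same incidence and severity "through passive surveillance in breastfed infants vs. not breastfed infants, by vaccine type and platform".
- **Exploratory 3, second endpoint:** the same "through passive surveillance in breastfed infants of individuals vaccinated during pregnancy vs. postpartum, overall and by vaccine type and platform".
- **Analysis, identical for both objectives:** "Incidence rates and 95% CIs will be calculated in Groups 2 and 4".

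Titers on the same mothers and infants appear in other rows. Primary 3 has "GMT of serum IgG ELISA and Neut antibodies at birth (cord blood) and at approximately 2 and 6 months of age in all infants". Secondary 7 has infant serum titers at about 2 and 6 months for the postpartum cohort. Secondary 5 has "GMT of IgG and immunoglobulin A (IgA) ELISA and Neut antibodies in breast milk at approximately 2 weeks" and at 2, 6 and 12 months.

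**The concern.** Both objectives ask whether antibody protects infants. Answering that needs infants who differ in antibody level and an analysis that uses the level. In these two rows an infant with no detectable antibody counts the same as one with a high titer.

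Followed as written, a vaccination contrast and two contrasts among breastfeeding or vaccination-timing groups would be reported as antibody protection. Differences in household exposure, maternal infection or testing behaviour could produce such a result or mask a true antibody effect, and case finding is by passive surveillance. The article expects its results to inform policy and personal decisions and offers its design as a template, so the label could be carried forward.

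**Working it through.** Table 5 gives no sample size, event count or power for these objectives, so there is no figure of the plan to reproduce. The check is a reading of objective against contrast, followed by a precision estimate for the remedy.

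**Step 1. Objective against contrast.**

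| Objective | Contrast in the endpoint | What differs between the groups | Titer used |
|---|---|---|---|
| Exploratory 2: maternal antibody | Infants of vaccinated mothers vs external rates | Maternal vaccination, plus anything else separating the cohort from the outside population | No |
| Exploratory 3: milk antibody | Breastfed vs not breastfed | Feeding, with all its effects and correlates | No |
| Exploratory 3: milk antibody | Breastfed infants, mother vaccinated in pregnancy vs postpartum | Vaccination timing, hence transplacental as well as milk antibody | No |

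The count is 0 of 3 contrasts and 0 of 2 analysis cells with a titer. The first contrast also includes infants of mothers vaccinated postpartum, who cannot have received transplacental antibody from that vaccination.

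**Step 2. Does another row make the link?** The primary and secondary immunogenicity rows report GMTs, cord-to-maternal ratios and comparisons between strata. Secondary 2 sets maternal titers against an external correlate of protection, if one is available, and involves no infant outcome. No row of Table 5 relates a titer to infant infection.

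**Step 3. Are the data planned?** Yes. Infant and cord titers come from Primary 3 and Secondary 7, milk titers from Secondary 5, and infant COVID-19 from the Follow-up and Study outcomes sections. Two limits apply: milk collection is optional (Follow-up), and the infant serum endpoints in Table 5 stop at about 6 months.

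**Step 4. Precision of a within-cohort titer analysis.**

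- About 1000 participants (Methods), at 200 pregnant to 65 postpartum per vaccine type: 1000 × 200/265 ≈ 755 in the pregnancy cohort and 1000 − 755 = 245 postpartum. One infant per mother is assumed.
- Infant incidence over follow-up: assumed, 5-30%.
- SE of the log hazard ratio per SD of log titer ≈ 1/√events. The 95% CI factor is exp(1.96 × SE).

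| Infants | Events at 5% / 30% | SE | 95% CI factor |
|---|---|---|---|
| 755 (pregnancy cohort, pooled) | 37.8 / 226.5 | 0.163 / 0.066 | ×/÷ 1.38 to 1.14 |
| 245 (postpartum cohort, pooled) | 12.3 / 73.5 | 0.286 / 0.117 | ×/÷ 1.75 to 1.26 |
| 200 (one vaccine type) | 10 / 60 | 0.316 / 0.129 | ×/÷ 1.86 to 1.29 |

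The Methods wording leaves open whether the 1000 includes infants. If it does, there are about 500 × 200/265 ≈ 377 pregnancy-cohort infants, 18.9 to 113 events, and a factor of ×/÷ 1.57 to 1.20. The formula assumes complete titers and no loss of information from adjustment, so actual intervals would be somewhat wider.

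**The case against.** **The objectives are exploratory and descriptive, and Table 5 shows openly what is compared.** This stands as a limit on weight: neither objective drives the sample size or a formal test. It does not remove the mismatch, because a descriptive result must still describe what its label says.

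**Details are left to a SAP that is not shown.** True, and the choice of model, time scale and covariates belongs there. But the Statistics section says that Table 5 outlines the analysis for each endpoint, and objective and contrast are both fixed there. A reader might infer that no titer-to-infection analysis will ever be done. The document does not support that; it shows only that Table 5 contains none.

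**The plan will seek to adjust for confounders.** This could help the breastfeeding contrast. It is unlikely to help a comparison with aggregate external rates, and no adjustment turns vaccination or feeding status into an antibody level.

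**All mothers in the cohort are vaccinated, so breastfeeding is a rough proxy for milk antibody.** Fair, but a proxy that also carries every other effect of breastfeeding cannot support a statement about antibody.

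**Cord titer alone would be a poor replacement.** This stands. Cord blood cannot carry antibody from a postpartum vaccination, and one birth titer ignores waning over 12 months. The change proposed here takes both into account.

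**Conclusion.** The mismatch is real and can be read directly from Table 5: two objectives about antibody, three contrasts, no titer. It should be corrected, with modest weight because the objectives are exploratory.

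Two stronger readings are not supported. One is that the study makes no use of titers; most primary and secondary endpoints are titers, and the gap is confined to Exploratory 2 and 3. The other is that these contrasts would necessarily show protection if antibody did nothing; that requires groups to differ in exposure or testing in ways left unadjusted, which is plausible but not shown.

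The mismatch itself rests on no assumption. The precision quoted for the added analysis, about ×/÷ 1.38 to 1.14 in the pooled pregnancy cohort, rests on the assumed 5-30% incidence, about 755 infants and complete titers. Within one vaccine type it would be weak. No figure can be given for the milk analysis, because uptake of the optional sampling is unknown.

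**What to change.** 1. In Table 5, label the three incidence comparisons as vaccination, breastfeeding and vaccination-timing contrasts, and state that they will not be reported as antibody effectiveness.
2. Add to each objective a within-cohort analysis relating infant laboratory-confirmed COVID-19 to measured antibody, pooled over vaccine types and accounting for calendar period.
   - **Exploratory 2:** in infants of mothers vaccinated in pregnancy (Group 3), cord titer updated by the 2- and 6-month infant serum titers; in infants of mothers vaccinated postpartum (Group 4), the 2- and 6-month serum titers alone.
   - **Exploratory 3:** the most recent milk titer among breastfed infants with milk samples, adjusted for infant serum or cord titer.
3. Leave the model specification to the SAP.
4. In the same edit, reconcile a separate error: both analysis cells name Groups 2 and 4, but the group list defines Group 2 as postpartum women and Groups 3 and 4 as the infants.

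Cost: wording in Table 5 and the SAP and one regression per objective, with no new samples. The added analyses remain observational and exploratory. The milk analysis covers only women who give optional samples, and months 6 to 12 rest on infant titers no later than about 6 months. If the added analyses are not wanted, step 1 with both objectives reworded to match is the minimum.

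### Exploratory objective 3 places a comparison by timing of maternal vaccination under a breast milk objective, although the two arms also differ in transplacental antibody and start of observation

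*Protocol article*

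**What the plan says.** All of the following is in the protocol article, mainly in the Statistics section.

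- **Objective.** Exploratory objective 3 in Table 5 is "To describe the effectiveness of breast milk antibodies to provide protection against SARS-CoV-2 infection/symptomatic disease/severity in infants" over the first 12 months of life.
- **First endpoint.** Incidence and severity of laboratory-confirmed COVID-19 "in breastfed infants vs. not breastfed infants, by vaccine type and platform".
- **Second endpoint.** The same outcomes "in breastfed infants of individuals vaccinated during pregnancy vs. postpartum, overall and by vaccine type and platform".
- **Analysis cell.** "Incidence rates and 95% CIs will be calculated in Groups 2 and 4".
- **Group list.** Group 2 is women vaccinated postpartum (up to 65 per vaccine type). Group 3 is infants of women vaccinated in pregnancy (about 200 per type). Group 4 is infants of women vaccinated postpartum (about 65 per type).
- **Transplacental pathway.** Primary objective 2 is "To describe the transplacental antibody transfer of SARS-CoV-2 antibodies among individuals vaccinated during pregnancy, overall and by vaccine type and platform". Primary objective 3 follows the antibody in these infants "at birth (cord blood) and at approximately 2 and 6 months of age in all infants". For the postpartum cohort, Secondary objective 7 measures infant serum "at approximately 2 and 6 months of age in infants of postpartum individuals, overall and by vaccine type and platform", with no cord blood in the endpoint.
- **Start of follow-up.** The Abstract and the opening of Methods start infants of the pregnancy cohort at birth. Infants in the postpartum cohort start when the mother enrols, within about 2 months of delivery.
- **Confounding.** The Statistics text allows covariate adjustment where it is judged appropriate. It names no antibody covariate.

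**The concern.** The objective asks what milk antibody does for the infant. An endpoint that serves it should vary exposure to milk, or to milk antibody, and hold the other maternal antibody route as constant as possible. The second endpoint does the reverse: it fixes breastfeeding and varies the timing of maternal vaccination, which determines whether the infant could also receive vaccine-induced antibody before birth.

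If incidence were lower after vaccination in pregnancy, Table 5 would have it reported as evidence on breast milk. If incidence were equal, a real difference in milk protection could be masked. The Background says that the results are meant to inform policy and personal decisions and that the design is offered as a template, so a mislabelled contrast could be misread and copied.

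**Working it through.** No sample size, event rate or effect size is attached to this objective, so there is no planned figure to reproduce. The check sets the rows side by side and then shows the consequence.

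**1. What differs between the arms of the second endpoint**

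| Feature | Mother vaccinated in pregnancy | Mother vaccinated postpartum |
|---|---|---|
| Breastfed | yes | yes |
| Antibody from that vaccination across the placenta | possible (Primary 2 and 3) | not possible, vaccination follows delivery |
| Start of infant observation | birth | enrolment, up to about 2 months |
| Milk antibody level | measured (Secondary 5) | measured (Secondary 5), may differ |

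Milk is one of three differences, and not the one that defines the arms.

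**2. What the contrast estimates**

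On a multiplicative scale, pregnancy versus postpartum:

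observed rate ratio = RR(transplacental) × RR(milk difference) × RR(other, including start of observation)

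One observed ratio cannot be split into these factors.

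**3. Illustration.** The values are assumptions; the documents give no infant protection figures. RR(other) is set to 1.

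- No milk difference, transplacental reduction of 20%, 40% or 60%: 0.80 × 1 = 0.80; 0.60 × 1 = 0.60; 0.40 × 1 = 0.40. All of it would appear under the milk objective.
- Milk protection better after postpartum vaccination, RR(milk) = 1.25, with a transplacental reduction of 20%: 1.25 × 0.80 = 1.00. A real milk difference would be invisible.

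**4. Can the second endpoint be computed from the groups named?**

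The cell names Groups 2 and 4. By the group list, Group 2 contains women and Group 4 the postpartum-cohort infants. The pregnancy-cohort infants are Group 3, which the cell omits, so the contrast cannot be formed from the groups named. Exploratory 1, on maternal infection, cites Groups 1 and 3, and Secondary 6, on women vaccinated postpartum, cites Group 3. Some rows thus appear to number women 1 and 3 and infants 2 and 4. That suggests both infant cohorts were intended here, but this is an inference.

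**The case against.** The strongest reply is that the objective is exploratory and descriptive, no test or decision depends on it, and the first endpoint addresses milk more directly. The Statistics text also allows adjustment and defers detail to an analysis plan. The points on exploratory status and on the first endpoint stand, and they keep the severity low. The adjustment sentence helps little with this particular factor: vaccine-induced transplacental antibody is nearly determined by cohort, so there is little overlap on which to adjust. Conditioning on infant serum titre at about 2 and 6 months would be possible, but the row does not state it.

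Three stronger readings are tempting and are not supported:

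- **That the second contrast holds no information on milk**, so that any effect found is timing and transplacental antibody. Both arms being breastfed does not make their milk antibody equal. Secondary 5 measures milk antibody after vaccination in pregnancy or postpartum, and it may differ. The contrast is a mixture, not empty of milk.
- **That the first endpoint pools infants across the two vaccination timings.** Table 5 does not say so. Read literally, the only infants in the analysis cell are Group 4, which is a single timing. If Groups 3 and 4 were meant, naming two groups still does not establish pooling.
- **That the analysis is fixed as crude incidence.** A one-line cell in a condensed article, next to a general adjustment sentence, does not establish that.

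**Conclusion.** The point holds for the second endpoint of Exploratory objective 3. The contrast mixes the transplacental route, start of observation and any difference in milk antibody, and its result cannot be credited to milk in either direction. This follows from the protocol's own definitions and needs no numerical assumption. The rate ratios of 0.80 to 0.40, and the masked result of 1.00, only illustrate size under assumed values. Separately, the analysis cell names the wrong groups for this contrast. The objective as a whole is not lost, because the first endpoint can serve it if it is analysed within cohort. Severity is low.

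**What to change.** 1. Move the pregnancy-versus-postpartum contrast out of the breast milk objective, for example to Exploratory 2 on maternal antibodies. Alternatively, keep it and label it as the combined transplacental-plus-milk association with timing of maternal vaccination, noting the different start of observation.
2. Answer the milk objective by comparing breastfed with not-breastfed infants within Group 3 and within Group 4 separately, then combining across the two strata.
3. Correct the analysis cell so that it names the two infant cohorts under the printed group list, Groups 3 and 4.

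This changes wording in Table 5 and the analysis plan and needs no new antibody data. The form of any regression model is analysis-plan detail.

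The cost is wider intervals within strata. As an illustration for one vaccine type, assume 20% of infants not breastfed and 15% infected; the documents give neither figure. The factor either side of the rate ratio is exp(1.96 × √(1/a + 1/b)), with a and b the case counts.

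- **Group 4:** 65 infants, 52 breastfed and 13 not, about 8 and 2 cases: exp(1.96 × √(1/8 + 1/2)) = 4.7.
- **Group 3:** 200 infants, 160 and 40, so 24 and 6 cases: exp(1.96 × √(1/24 + 1/6)) = 2.4.
- **Combined by inverse variance:** weights 1/0.625 = 1.6 and 1/0.2083 = 4.8, so exp(1.96 × √(1/6.4)) = 2.2.

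With half or double the cases, Group 4 gives 8.9 or 3.0, Group 3 gives 3.5 or 1.9, and the combination gives 3.0 or 1.7. With so few cases the formula is rough. These factors describe precision, not the bias discussed above. Group 4 alone would say little for a single vaccine, which is why the strata should be combined after being shown separately. Stratifying removes the cohort difference; it does not remove other differences between mothers who breastfeed and those who do not.
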